Lifestyle interventions have been shown to be effective in the reduction of body weight [8] and cardiometabolic risk factors such as waist circumference, triglycerides and fasting glucose in adults with SMI [9, 10]. However, the quality of studies on the effectiveness of lifestyle interventions in the SMI population is rather low, samples are small and results are inconsistent [10, 11], although one well-designed relatively large intervention RCT has recently been published [12]. Systematic reviews on lifestyle interventions in different populations indicate that, to be effective, a lifestyle intervention should contain at least three key components: exercise, diet and behavioural therapy [11]. Behavioural therapy strategies that enhance individual behavioural change include improving self-management skills such as tailoring information to the individual, identifying (lifestyle) areas for improvement, goal setting, making action plans, giving personalized feedback to reinforce new behaviours and using social and environmental strategies to support change [13, 14]. However, most of these techniques have a limited effect, and only work well for patients who are motivated [15]. An approach to deal with unmotivated patients or patients who are not ready to change yet, is the motivational interviewing (MI) approach of Miller and Rollnick [16] combined with the stages-of-change from the transtheoretical model of Prochaska and DiClemente [17]. MI is a patient-centred counselling approach that targets behaviour change by addressing intrinsic motivation. MI seems more effective than traditional methods in targeting lifestyle change [18]. It has been shown to be effective in improving weight status, Body Mass Index (BMI) and cholesterol levels of overweight and obese adults and of clients in a broad range of other domains [19, 20]. According to the stages-of-change from the transtheoretical model, patients’ level of motivation and self-efficacy to change is reflected in one of the five stages of change [21, 22]: the precontemplation, contemplation, preparation, action or maintenance stage, ranging from no intention to change till the motivation to maintain behaviour change. Treatment (or intervention) should adapt to a patient’s stage-of-change in order to increase intrinsic motivation for behaviour change [21]. A combination of action planning with feedback and a motivational stages-of-change approach is believed to be effective in behavioural change in SMI patients [23]. In addition, mental care is nowadays more rooted in the community and therefore more depending on SMI patients’ peers, families and environment. Therefore, peer and family support is considered an essential component for successful intervention implementation.

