### Intervention

The intervention in this trial is a 12-month multidimensional, patient-centred lifestyle intervention, including use of the web tool ‘Traffic Light Method for somatic screening and lifestyle’ (TLM), which supports behaviour change in various phases. The five most important features of the intervention are presented in Table 1.

**Table 1 Tab1:** Five important features of the multidimensional lifestyle intervention using a web tool in the LION study

Feature	Description
1	Patients’ readiness for behaviour change is not a prerequisite for starting the intervention. Nurses encourage behaviour change by making use of the stages-of-change of the transtheoretical model [17] and motivational interviewing [16].
2	Patient-centeredness: patients decide if and what behaviour he/she wants to change, creates his/her own lifestyle plan with realistic goals and support. The tool can also be used by patients themselves to enhance self-management.
3	Because diet and physical activity are key components of a healthy lifestyle, these components are combined with behavioural change counselling; for an intervention to be effective, these three ingredients should be included [11].
4	Active support of the patient’s family and friends, incorporated in the lifestyle plan.
5	Nurses are trained to not only support patients in their behaviour change but also work behind the scenes to create a healthier environment: organise accessible exercise opportunities, raise team support for a healthier lifestyle in patients and share up to date lifestyle knowledge with the team, and raise awareness among other health care professionals (e.g. GP’s) of the increased cardiovascular risk of most SMI patients.

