### Statistical analysis

Variables will be presented as mean ± standard deviation (SD), and if not normally distributed as median [25th-75th percentiles], or N (%) for frequencies. Missing data are handled differently based on amount and type of missingness. If missing data can be well predicted by regression methods, multiple imputation will be considered. Otherwise, interpolation or replacement by study mean or median will be preferred over complete case analyses.

The primary outcome is the change in waist circumference (in cm) over time (from baseline to six and from baseline to twelve months) comparing the intervention group to the control group. This will be analysed with multilevel linear mixed models using teams as cluster. Analysis will be based on intention-to-treat principle. In per-protocol analyses, the intervention effect on cardiometabolic risk factors will be studied as described above, comparing participants with different degrees of intervention adherence to controls. Secondary study outcomes are analysed according to the same principles and techniques as the primary outcome. A priori sensitivity analyses are foreseen for participants’ age, gender and type of housing. In additional analyses, we will test whether the 12-months lifestyle intervention changes the level of motivation (stage-of-change) for changing diet of physical activity levels. An alpha of 0.05 is considered statistically significant.

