### Potential risks for bias

Some potential risks for bias might be expected. First, although patient selection bias should be minimal, it is still possible that it is difficult for nurses to include patients that are unmotivated to change their lifestyles in a lifestyle intervention study. Motivated patients are expected to be more easily included, leading towards patient selection bias based on the level of motivation. Second, because patients determine which lifestyle behaviours they wish to change, it is possible that they target other somatic health outcomes (e.g. dental health, sleeping patterns) than the primary study outcome waist circumferences and other cardiometabolic risk factors. In this case, stating that the intervention does not seem effective in reducing the primary outcome might be a biased conclusion when patients wished to change other health outcomes and might have been successful in addressing these changes. Third, although ROM is implemented on all sites, it is possible that not all sites have the capacity to conduct all measures, leading to missing values. In addition, ROM nurses cannot collect blood samples themselves but send patients an invitation to visit a (hospital) laboratory. Although ROM nurses convince and remind patients to do so, patients might be reluctant to go to the laboratory, also leading to possible missing values.

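### The per-protocol analysis reads as an intervention effect a contrast between adherence-defined intervention patients and undivided controls, which randomisation does not protect

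*Protocol article*

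**What the plan says.** The Statistical analysis section sets the main analysis first: "Analysis will be based on intention-to-treat principle". For the model it says: "This will be analysed with multilevel linear mixed models using teams as cluster". It then adds a further analysis: "In per-protocol analyses, the intervention effect on cardiometabolic risk factors will be studied as described above", and completes that sentence with the contrast, "comparing participants with different degrees of intervention adherence to controls".

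Three things are thus fixed: the target (the intervention effect), the model (the team-clustered mixed model) and the groups to be compared. No restriction of the control group is mentioned, no predictor of adherence is named for adjustment, and the analysis is not labelled exploratory.

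The Control group section states that control patients make no lifestyle plan and so have no biweekly follow-up sessions. Table 1 under Intervention says "Patients’ readiness for behaviour change is not a prerequisite for starting the intervention", and that patients themselves decide whether and what to change.

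**The concern.** Adherence to the sessions is defined only in the intervention arm and becomes known only after allocation. Splitting that arm by adherence and setting each part against all controls compares a selected group with an unselected mixture. Any patient or team characteristic that predicts both adherence and the course of waist circumference then enters the estimate.

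Several such characteristics are plausible here. Readiness to change is not required at entry, so motivation can vary. Illness severity may limit attendance and engagement. The Background and the section on changes in study design describe high nurse workload and competing priorities, so adherence may also reflect how well a nurse or team delivered the programme.

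What is at stake is the reading of the supplementary result. A difference between high adherers and controls, reported as an intervention effect, could be taken as evidence that the programme works when followed, although selection alone could have produced it.

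**Working it through.** **Stated design figure, as background.** From the Participants section: SD 16.3 cm, difference 5.8 cm, two-sided 0.05, about 80% power, 250 patients analysed. Assuming 1:1 allocation and no clustering:

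n per arm = 2 × (1.96 + 0.84)² × 16.3² / 5.8² ≈ 124, or 248 in total. Power with 125 per arm is 80.3%. The stated figure reproduces. The present point does not depend on it; 5.8 cm serves only as a yardstick.

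**Can the planned contrast recover an effect?** With zero true effect, each patient's change in waist circumference is what it would have been anyway. The two arms then have the same expected change, which is why intention-to-treat is safe. A subgroup of one arm chosen by adherence has that same expected change only if adherence is unrelated to the untreated change. Nothing in the design secures this, and no matching subgroup of controls can be formed.

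**Illustration of size.** Inputs, all assumed:
- true effect zero;
- intervention patients split into thirds by adherence;
- correlation c between adherence and the waist reduction that would have occurred anyway: 0.1, 0.2 or 0.3;
- SD of change: 5, 7.3 or 10.3 cm. The last two follow from 16.3 × √(2(1 − r)) with an assumed baseline to follow-up correlation r of 0.9 (7.3) or 0.8 (10.3). The 5 cm value is a lower assumption.

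The mean of the top third of a standard normal variable is 1.09. The spurious difference between the top third and all controls is c × 1.09 × SD of change. The bottom third shows the same amount in the opposite direction, and the middle third shows none.

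| SD of change | c = 0.1 | c = 0.2 | c = 0.3 |
|---|---|---|---|
| 5 cm | 0.5 cm | 1.1 cm | 1.6 cm |
| 7.3 cm | 0.8 cm | 1.6 cm | 2.4 cm |
| 10.3 cm | 1.1 cm | 2.2 cm | 3.4 cm |

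The range of 0.5 to 3.4 cm is 9% (0.545 / 5.8) to 58% (3.37 / 5.8) of the design difference.

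**False-positive rate in the same illustration.** Comparing 125/3 patients with 125 controls and ignoring clustering, the standardised shift is c × 1.09 / √(3/125 + 1/125) = c × 6.1, whatever the SD. For c = 0.1, 0.2 and 0.3 this is 0.61, 1.22 and 1.83. The chance of a nominally significant result is then about 9%, 23% and 45%, instead of 5%.

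**The case against.** The strongest reply is that the primary inference is untouched. Intention-to-treat is the stated basis and the per-protocol work is additional. That stands, and it limits the weight of the point. A reader might infer that the trial's main conclusion is compromised, or that the plan intends to claim benefit in adherent patients after a null result. The article says neither.

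A reader might also infer that the protocol itself shows motivated patients would improve untreated. It does not. The Background remark that "most of these techniques have a limited effect, and only work well for patients who are motivated" is about a larger effect of the techniques in such patients, not about their course without them. The sentence "Motivated patients are expected to be more easily included, leading towards patient selection bias based on the level of motivation" concerns who enters the trial; if mainly motivated patients enrol, motivation varies less within the sample and bias from that source would shrink. Nor do the documents support motivation as the sole confounder, since severity and delivery are equally open.

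The words dose-response and tertile are not in the article, and that all controls are used is read from the unqualified word controls. An unseen analysis plan could define the adherence groups and add covariates. That would help, but adjustment for measured baseline variables cannot identify the missing control adherers. The contrast and its interpretation as an intervention effect are already stated, so this is not merely an omitted detail.

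Finally, an instrumental-variable analysis is no clean replacement. Feature 5 of Table 1 has nurses changing the environment and team support outside the sessions, so allocation can act by routes other than logged sessions. With one binary instrument, the estimate is essentially the intention-to-treat difference rescaled by mean adherence, and it adds little after a null result. This is why it is proposed below as an addition with stated assumptions.

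**Conclusion.** The concern holds as a moderate point about a supplementary analysis. As written, the per-protocol comparison is presented as an intervention effect, is not protected by randomisation, and can give a graded difference across adherence levels with no true effect. The intention-to-treat result is not affected.

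The direction and size of the bias cannot be derived from the documents. The centimetre range and the false-positive rates rest wholly on the assumed correlation, SD of change and tertile split. They show that the bias need not be negligible; they are not a forecast of it, and the range should not be quoted as the expected error in this trial.

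**What to change.** 1. Stop describing the adherence-group contrast with controls as an intervention effect. Label it exploratory and non-causal, and define adherence before the outcome data are examined.
2. Adjust it for baseline predictors of adherence already collected, for example baseline waist circumference and stage-of-change. The screening questions in the web tool, which control patients also complete, include stage-of-change for diet and for physical activity. State that adjustment covers measured predictors only.
3. As the adherence-related effect estimate, add a complier-average causal effect with team allocation as the instrument, adherence taken from the follow-up reports logged in the web tool (none in controls), and standard errors clustered by team.
4. State two assumptions beside that estimate: that allocation acts only through the logged sessions, which is imperfect because nurses also work on the environment; and that the effect rises linearly with the number of reports.

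The cost is a change of wording, one extra model and confidence intervals wider than those of the simple contrast. The follow-up reports are already completed in the web tool under the Procedure section, so no new data collection should be needed.

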## Discussion

Given the disturbingly high levels of metabolic diseases in SMI patients, and the associated risks of premature death [1], it is of high importance to develop lifestyle interventions that can effectively be implemented in regular care. The current study investigates whether a multidimensional lifestyle intervention using a practical lifestyle tool for mental health nurses to improve their knowledge, skills and expertise regarding healthy lifestyle behaviours and behaviour change in severe mentally ill patients, influences cardiometabolic risk factors of SMI patients in their caseload. The Traffic Light Method (TLM) tool aims for patients to increase lifestyle behaviour awareness and knowledge, improve self-management (setting lifestyle goals, receiving systematically feedback) and to involve friends and family in achieving lifestyle goals. The primary outcome of the study is waist circumference, considered the best predictor of abdominal fatness and cardiovascular disease [52], and other cardiometabolic risk factors. These measures are strongly associated with a range of negative health outcomes, such as type 2 diabetes, stroke and cardiovascular disease [53, 54].

### Strengths of the intervention

The motivational interviewing approach is a major strength of this intervention as it enables inclusion of all patients, regardless of their motivation to change their lifestyle behaviours. Addressing the (lack of) motivation as part of the intervention has been proven successful in improving medication adherence in persons with schizophrenia [55], altering substance (ab)use [56] and weight loss in (overweight and obese) adults [19, 20]. Because the intervention is implemented during regular care visits by their own MH nurse, large numbers of patients can benefit from the intervention.

In the intervention, the patient is taking the lead in creating a lifestyle plan and determining his/her lifestyle goals. Therefore, every patient is able to direct the lifestyle intervention in such a way that it contributes to his/her specific recovery wishes. This fits well within the recovery approach in which patients take control over their own recovery process and decide themselves which (lifestyle) behaviours they wish or need to change in order to recover [57]. In the field of mental health, the recovery approach fits well because of the person-centeredness, focus on improving quality of life besides solely reducing impairments of the mental illness and the acknowledgment of multiple possible pathways to recovery.

Another advantage of using the TLM web tool is that it systematically addresses a broad range of lifestyle behaviours instead of solely focussing on diet or physical activity. This gives patients the option to choose which lifestyle behaviour they wish to change. In addition, health professionals have expressed that lifestyle interventions should at least include the following lifestyle topics: “(1) healthy eating; including buying healthy foods on a budget, cooking skills and recipes, (2) the risks of weight gain and how to monitor weight, (3) exercise; what is available, physically possible, affordable and accessible, (4) dental hygiene, (5) substance misuse and (6) physical health monitoring such as blood checks” (p. 402) [23]. All mentioned components are present in TLM, therefore it can be considered a complete and comprehensive lifestyle intervention tool.

A last strength of the intervention is that the web tool constitutes an objective source of information that draws the attention of both patient and MH nurse to unhealthy lifestyle behaviours by presenting a risk profile and showing related healthy options. The nurse coaches the patient in the behavioural changes he/she wishes to make using MI and the stages-of-change techniques. Therefore, the MH nurse will not impose unwanted lifestyle advices, which is a benefit for the professional relationship between nurse and patient.

### Strengths of the study design

The study design for this trial has several advantages. First, by using regular ROM screenings and structurally inviting all patients with screening outcomes indicating at least one cardiometabolic risk factor, patient selection bias is minimal. Second, the intervention is feasible for a large number of patients (e.g. also unmotivated patients are eligible, implementation during regular care visits), leading to a large and highly representative study sample to be included. Third, follow-up of less motivated patients is feasible because of the routine ROM screenings, which will be performed routinely in all patients. Fourth, data collection is based on existing Routine Outcome Monitoring screenings infrastructures, which has several advantages: ROM nurses are well trained, baseline and follow-up measures are conducted by the same nurse, and additional time and costs of patients, nurses and researchers are limited. The ROM data collection covers a wide scope of measures, i.e. several physical measures and multiple psychosocial measures and, for this trial, only had to be extended with cost-effectiveness measures. Finally, the pragmatic character of the study, in which MH nurses carry out the intervention in hectic real word health care settings, will result in realistic and achievable intervention outcomes, representing outcomes with high external validity [8, 13].

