### Study setting

Mental health care for severe mentally ill (SMI) outpatients is organized by a Flexible Assertive Community Treatment (FACT) team with MH nurses. FACT means that patient care is outreaching, takes place in the community (patients’ own environment) and ranges from high intensive (24 h) treatment to low intension support – for a detailed description of FACT, see [30, 31]. Patients living in sheltered facilities receive a combination of housing and services in the community. 21 FACT and eight sheltered facility teams serving SMI patients of five mental health care organizations in the North of the Netherlands, an area covering 2.8 million inhabitants, are invited for this study. Per team, nurses are invited to participate. All teams per organization are matched based on caseload size, mean age of patients, mean duration of admission of patients, most frequent diagnosis and location (urban or rural). After matching, teams are randomly allocated to the control or intervention arm by means of a random number generator by a researcher of the research team not involved in training of staff and recruitment of patients (see Fig. 1 for flowchart of the study). To minimise spill-over, randomisation is on team level, although inclusion of study participants and statistical inference are on patient level.

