### Participants

The study population consists of community-dwelling SMI patients and SMI patients living in sheltered facilities. Of this population, approximately 75% of the patients is diagnosed with a psychotic disorder, 15% with bipolar disorder and approximately 10% with complex personality disorders. In the North of the Netherlands, SMI patients are invited for annual Routine Outcome Monitoring screenings as part of standard care, consisting of a physical examination, a lab test and psychosocial measures. Patients are invited for the LION study when ROM screening outcomes indicate at least one of the following risk factors for metabolic syndrome: waist circumference > 88/102 cm (females/males); fasting glucose > 5.6 mmol/L or HbA1c > 5.7%; BMI > 25 kg/m^2^. Exclusion criteria are being pregnant, a BMI < 19 kg/m^2^, being primarily diagnosed with Korsakov syndrome or having a physical impairment which makes daily physical activity impossible. When patients are eligible for the study, they receive a detailed information letter from their case manager and, if willing to participate, sign informed consent.

The main objective of this trial is to detect an abdominal weight loss having public health significance. Previous work has indicated that 5-10 cm reduction in waist circumference (WC) is considered a realistic guideline with a high probability of health benefits [32]. For power calculations, we assumed 10% dropout rate. To include 250 participants, a 10% extra will be needed resulting in a total of 275 patients. Under these assumptions, and assuming an SD of 16.3 cm based on pilot data from this population, for two-sided 0.05-level tests of the null hypothesis, the study should provide approximately 80% power for detecting a difference of 5.8 cm in WC at 12 months between intervention and control groups. In addition, the study will have the same power to detect a reduction of 0.6 mmol/L in plasma glucose, given an SD of 1.7 mmol/L.

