The 12-month intervention will be delivered by MH nurses. Before the start of the study, nurses will receive one day of training on (a) basic components of motivational interviewing [16] and the stage of change model [33], (b) side effects of psychotropic medication, (c) lifestyle of and risks for SMI patients, (d) working with TLM, and (e) environmental factors that affect effectively working with TLM (e.g. health behaviour of staff members themselves or the availability of unhealthy products in the home environment) – see Meijel (2015) [25] for more details. In addition, the study protocol will be explained. After three months, an evaluation session is planned to discuss obstacles with the tool, obstacles in motivating patients to participate and to recollect study protocol. Trained LION nurses are, due to the nature of the intervention, not blind for study allocation.

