#### Measurements on patient level

Most measures on patient level are conducted during the ROM screening, which is part standard care and of the scientific ongoing PHAMOUS (Pharmacotherapy Outcome and Monitoring Survey) cohort [34]. In mental health care organisations in the North of the Netherlands, it is routine care that ROM trained nurses invite patients annually for a ROM screening including somatic and psychosocial measures. Data of these measurements are reported in patients’ record forms and discussed with the patient. These data are stored in a large database and anonymized data are available for scientific research. This method was approved by the Medical Ethical Committee of the University Medical Center Groningen. For the LION study, data of two regular ROM screenings will be used for baseline and 12-months measures. An additional, short version of the ROM screening is scheduled six months after start of the intervention and patients will receive a small fee (€5,00/£4,30) for participation. ROM nurses carrying out the assessments are blinded for study allocation.

General data on birth year, gender, diagnosis, duration of illness and use of medication are derived from patient record forms.

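### Patients appear to be asked for consent after their team's allocation is known, so selection may differ by arm and the claim of minimal selection bias is not supported

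*Protocol article*

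**What the plan says.** Under Study setting, teams are matched within organisation and then randomised: "After matching, teams are randomly allocated to the control or intervention arm by means of a random number generator". This is done "by a researcher of the research team not involved in training of staff and recruitment of patients". The same section states that "randomisation is on team level, although inclusion of study participants and statistical inference are on patient level".

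Under Participants, patients whose Routine Outcome Monitoring (ROM) screening crosses fixed thresholds are eligible; "they receive a detailed information letter from their case manager" and then decide on informed consent. Under Intervention, nurses are trained before the study starts and trained nurses are not blind. Three months later a session covers, among other things, "obstacles in motivating patients to participate and to recollect study protocol". Under Control group, control patients answer the lifestyle questions in a blank version, with no feedback, no lifestyle plan and no biweekly follow-up.

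The Discussion (Strengths of the study design) concludes that, by "structurally inviting all patients with screening outcomes indicating at least one cardiometabolic risk factor, patient selection bias is minimal". The next section, Potential risks for bias, repeats that selection bias should be minimal and then concedes: "Motivated patients are expected to be more easily included, leading towards patient selection bias based on the level of motivation".

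**The concern.** In a cluster trial, randomising teams protects the comparison only if the patients who enter do so independently of their team's arm. Here the staff who approach patients work in teams whose allocation is apparently already known, and patients are asked to join different things: coaching with biweekly follow-up in one arm, a blank questionnaire and usual care in the other. The work per enrolled patient also differs, at about 15 minutes every two weeks against none.

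If the kind of patient who agrees differs by arm, the arms differ from the start on something that may affect the change in waist circumference. The primary comparison is then biased, however well waist is measured. The article treats selection on motivation as a matter of who enters the trial overall, which bears on generalisability. It does not say that the selection may differ between arms, which bears on internal validity.

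**Working it through.** **Order of events, assembled from the sections**

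| Step | Section | What follows |
|---|---|---|
| Teams matched and randomised | Study setting | Allocation fixed for the whole team |
| Nurses trained before study start, not blind | Intervention | Intervention staff know the arm by then |
| Letter from case manager, then individual consent | Participants | Approach and consent happen inside the team |
| Different content by arm | Control group | Patients are asked to join different programmes |
| Nurses described as including patients | Potential risks for bias; Changes in study design | Recruiters are team staff |

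No section describes concealment of allocation from the recruiting staff or from patients at consent.

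**Do the stated safeguards cover this?**
- The independent randomising researcher protects the sequence of teams, not the later recruitment of patients.
- Blinded ROM nurses protect measurement.
- Matching uses team characteristics (caseload, mean age, mean duration of admission, diagnosis, location), not the motivation of those who consent.
- Intention-to-treat and the mixed model with teams as cluster (Statistical analysis) analyse whoever enrolled. Analysing change does not help if motivation affects the change itself.
- Inviting all patients who meet the criteria acts at invitation, not at consent.

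**The plan's own figure.** Inputs from Participants: 250 evaluable patients, taken as 125 per arm; SD 16.3 cm; difference 5.8 cm; two-sided 0.05; no clustering.
- SE = 16.3 × √(2/125) = 2.06 cm
- 5.8 / 2.06 = 2.81; power = Φ(2.81 − 1.96) = 0.80

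The stated power of about 80% is reproduced and is not in dispute.

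**Illustrative bias.** The article gives none of these inputs; all are assumptions.
- Bias = (difference between arms in the share of motivated patients) × (extra waist change in motivated patients without the intervention)
- 0.20 × 3 cm = 0.6 cm; 0.40 × 3 cm = 1.2 cm
- Other choices: 0.10 × 3 = 0.3 cm; 0.30 × 8 = 2.4 cm

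Against the 5.8 cm target: 0.6/5.8 = 10%; 1.2/5.8 = 21%.

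If the baseline to 12-month correlation is assumed to be 0.8, the adjusted SE is 2.06 × √(1 − 0.8²) = 2.06 × 0.6 = 1.24 cm.

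Rejection rate with no true effect = 1 − Φ(1.96 − bias/SE) + Φ(−1.96 − bias/SE):

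| Bias | SE 2.06 cm | SE 1.24 cm (r = 0.8 assumed) |
|---|---|---|
| 0.6 cm | 0.29 SE; 6.0% | 0.49 SE; 7.7% |
| 1.2 cm | 0.58 SE; 9.0% | 0.97 SE; 16.3% |

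**The case against.** **The order is not stated in one place.** This stands as a limit. The flowchart is not shown, and that case managers know the allocation is inferred from team-level randomisation and unblinded trained nurses. The three-month session is weak evidence that recruitment continues after training, because participating may mean engaging with the tool. The inference still rests on training before study start and on individual consent within teams.

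**Fixed thresholds and inviting everyone leave no room for selection.** This stands for invitation. A reader might infer that staff choose whom to invite differently by arm; the article does not support that. The open point is consent.

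**The article already concedes the risk.** Partly. It expects selection on motivation, which already sits badly with *minimal*, but it does not say that the arms may differ.

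**Direction and size are unknown.** This stands. Nurses trained in motivational interviewing might enrol more unmotivated patients, which could mask a benefit. On the article's own SD, 1.2 cm is 0.58 of a standard error; only the assumed correlation of 0.8 brings it close to one.

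**Other stronger readings.** A reader might infer that control staff receive no recruitment briefing; the article says only that they give care as usual. Nor does it give 29 as the number of teams randomised: 29 were invited.

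**Post-randomisation recruitment is the price of limiting spill-over.** Fair as a reason for the design, but it does not make the claim of minimal bias correct.

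**Conclusion.** The point holds as a risk that the design leaves open and the text denies. As described, recruitment is not protected from knowledge of allocation, so selection at consent may differ by arm. The word *minimal*, used in both Discussion sections, is not supported.

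It would go too far to conclude that the arms are imbalanced or that the result will favour the intervention: nothing in the article shows an imbalance or its direction. The 0.6 to 1.2 cm is illustrative only. It depends on the assumed 3 cm and 20 to 40 points, and its weight relative to the standard error depends on whether a baseline correlation of 0.8 is assumed. The conclusion about the wording needs none of these figures. It rests on the inferred order of allocation, training and consent.

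**What to change.** 1. **Wording.** In Strengths of the study design and Potential risks for bias, replace *minimal* with a statement that recruitment may differ by arm, in an unknown direction. Cost: a few words.
2. **Teams not yet recruiting, if any.** Identify eligible patients by the fixed ROM criteria and obtain consent before allocation is released to the team. Inviting first is not enough if consent follows release. Cost: later release of allocation and later training for those teams.
3. **All teams.** Compare eligible, invited and consenting patients by arm on baseline ROM values. Compare baseline stage-of-change for diet and physical activity by arm. It is among the web-tool questions (Table 2), and control patients fill in that part too. Add a sensitivity analysis adjusting the waist effect for baseline stage-of-change and baseline waist. Cost: a recruitment log and one extra model. Limit: stage-of-change is recorded after consent, with feedback in one arm and a blank form in the other, so it captures motivation imperfectly.
4. **If the routine data can be linked to team and date.** Add a supportive analysis of 12-month waist in all ROM-eligible patients of the randomised teams, whether or not they consented. The article says "anonymized data are available for scientific research" but does not describe such linkage. State that the effect is diluted by non-consenters and by patients of non-participating nurses, and that ROM data will be incomplete. This analysis supports the primary one and does not replace it. Cost: one data extraction, with no new visits.
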